# Outcomes of community-based differentiated models of multi-month dispensing of antiretroviral medication among stable HIV-infected patients in Lesotho: a cluster randomised non-inferiority trial protocol

**DOI:** 10.1186/s12889-018-5961-0

**Published:** 2018-08-29

**Keywords:** Differentiated models of care, Antiretroviral therapy, HIV, Retention, Virologic suppression, Cost-effectiveness, Lesotho

## Abstract

**Background:**

Current World Health Organization (WHO) guidelines recommend early initiation of HIV positive patients on antiretroviral therapy (ART) irrespective of their clinical or immunological status known as the test and start approach. Lesotho, like many other countries introduced this approach in 2016 as a strategy to reach epidemic control. There will be rapidly growing number of HIV-infected individuals initiating treatment leading to practical challenges on health systems such as congestion, long waiting time for patients and limited time to provide quality services to patients. Differentiated models of ART delivery is an innovative solution that helps to increase access to care, while reducing the burden on existing health systems. Ultimately this model will help to achieve retention and viral suppression. We describe a demonstration study designed to evaluate a community-based differentiated model of multi-month dispensing (MMD) approaches of ART among stable HIV patients in Lesotho.

**Methods:**

This study will be a three-arm cluster randomised trial, which will enrol approximately 5760 HIV-infected individuals who are stable on ART in 30 selected clusters. The clusters, which are health facilities, will be randomly assigned into the following differentiated model of care arms: (i) 3 monthly ART supply at facilities (Control), (ii) 3 monthly ART supply through community ART groups (CAGs) and (iii) 6 monthly ART supply through community ART distribution points (CAD). Primary outcomes are retention in care and virologic suppression, and secondary outcomes include feasibility and cost effectiveness.

**Discussion:**

Important lessons will be learnt to allow for improved implementation of such demonstration projects, including various needs for reliable supply of medication, access to quality clinical data including access to viral loads (VLs) results, frameworks to support lay worker cadre, involvement of community stakeholders, and reliable data systems including records of key indicators. MMD will have positive implications including improved retention, virologic suppression, convenience and access to medication.

**Trial registration:**

ClinicalTrials.gov Identifier: NCT03438370. Accepted on 16 February 2018.

**Electronic supplementary material:**

The online version of this article (10.1186/s12889-018-5961-0) contains supplementary material, which is available to authorized users.

## Background

Lesotho is undergoing a significant health transition characterised by high burden of infectious diseases such as HIV/AIDS, tuberculosis and an emergence of non-communicable diseases [1]. Among adults, HIV prevalence in Lesotho is reported to be 25% and 53% of adults are receiving antiretroviral treatment (ART) [2]. An estimated 310,000 people were living with HIV and 18,000 died from AIDS related issues in 2015 [3]. PEPFAR adopted the UNAIDS 90–90-90 targets and the new WHO guidelines on when to initiate ART [4]. The WHO guidelines recommend ART initiation immediately after testing positive, regardless of CD4 count, with lifelong continuation to warrant and improve individual ‘s health and reduce HIV transmission [5]. To realize the full benefits of this approach, high levels of adherence and retention are needed. In low to middle income countries (LMICs) including Lesotho, long waiting times in ART clinics, cost of travel to clinics and other life commitments are known to disrupt and reduce the adherence and retention levels. A need for monthly dispensing and/or systems that require multiple separate visits for refills and clinical evaluations can raise significant challenges for people living with HIV (PLHIV) and result in treatment interruptions or complete disengagement from care [6]. Hence, extending of interval ART refills may improve outcomes, if supply can be guaranteed for up to six months for stable patients in low resourced settings.

Currently, many LMICs including Lesotho dispense ART monthly which places demands on the health system and can lead to suboptimal adherence and disengagement in care due to the time and cost of frequent visits to clinic. There is need to implement novel strategies for ART dispensing to enable health systems cope with the ever-increasing number of HIV patients needing care and treatment. A gap exists in allowing stable patients to have an adequate and longer-term supply of ART especially if this does not compromise outcomes of interest including retention and viral load (VL) suppression.

Community based models of care i.e. CAGs are postulated to further strengthen adherence, retention and viral suppression. These models give peer support among patients. CAGs have been successfully implemented in Lesotho and introducing MMD into them can have the same intended outcomes as facility-based interventions, whilst additionally decongesting and decentralising facilities.

Potential benefits for this approach includes (i) higher adherence to ART and retention in care, (ii) reduced per-patient cost of providing ART, by reducing the number of clinic visits required, (iii) decongestion of clinics to allow for increased capacity to manage patients newly diagnosed with HIV, those with infectious complications, treatment failure, and other co-morbidities and (iv) decreased waiting time and improved efficiency at clinics allowing for improved quality of care and patient satisfaction [7, 8].

Limited data are available from LMICs on multi-month scripting and dispensing and on studies using community-based models of care. A review of the literature reveals a lack of randomized studies of different ART dispensing intervals. An abstract presented at the Conference on Retroviruses and Opportunistic Infections, 2016 using Zambian data, suggested that requirements for monthly dispensing and/or systems that require multiple separate visits for refills and clinician evaluation can raise significant challenges for people living with HIV and result in treatment interruptions or complete disengagement from care [6].

This study’s primary objectives are (i) to determine if stable patients receiving 3 monthly dispensing of ART within CAGs have non-inferior retention in care and viral load suppression than stable ART patients receiving 3 monthly dispensing at health facilities after 12 and 24 months, (ii) 6 monthly dispensing of ART within the community from a health care worker have non-inferior retention in care than stable ART patients receiving 3 monthly dispensing at health facilities after 12 and 24 months and (iii) 6 monthly dispensing of ART within the community from a healthcare worker have non-inferior retention in care than stable ART patients receiving 3 monthly dispensing within CAGs after 12 and 24 months. The secondary objectives are to compare cost outcomes (cost per patient retained and cost per patient retained with viral suppression) between the three models, investigate the acceptability of 3 and 6 monthly community-based ART distribution among patients and service providers and to assess if there are measurable gains in clinic productivity realized following the introduction of community based MMD of ART.

## Methods/design

### Setting

This study will include 30 health facilities (clusters) purposely selected from Maseru, Mafeteng and Mohale’s Hoek districts. These districts have been purposively selected due to (i) high numbers of patients on ART, (ii) has established and have since prioritised CAGs (iii) ability to perform VL determination as part of routine care. Facilities are to be included in the study if they have implemented or have systems in place for CAGs or community ART dispensing (CAD) through a healthcare worker, CAGs and CAD points are feasible within the health facilities community, health facility routine data collection and systems are in place, completeness of medical records, ability to perform VL determination as part of routine care, existing drug supply chain procedures for multi-month dispensing, and a large enough population to enrol stable ART patients.

### Study design

The study will be a pragmatic, three arm, parallel, cluster-randomized non-inferiority design. The thirty facilities (clusters) will be randomly assigned to three arms (Fig. 1) with patients receiving (i) 3MF- 3 monthly ART supply at facilities (Control), (ii) 3MC - 3 monthly ART supply through community ART groups (CAGs) and (iii) 6MCD - 6 monthly ART supply through community distribution points (CAD). Included facilities will be randomized, with stratification by whether the facility is in a rural or urban setting according to the Lesotho Bureau of Statistics’ data. After this process, each arm will, contain 10 facilities.

**Fig. 1 Fig1:**
[figure not shown]
Multi-Month Community Dispensing of ART: Examining the Role of Differentiated models of ART Supply on Retention and Virologic Suppression

### Study population and eligibility

This study will be conducted among approximately 5760 HIV-infected individuals who are stable on ART in 30 selected clusters. The eligibility criteria of participants are tabulated in Table 1.

**Table 1 Tab1:** Eligibility criteria for participants

To be included are those:	
(i) 18 years of age or older and willing to provide written informed consent,	
(ii) willing to participate in the MMD model (arm) that the patient’s study cluster has been randomized to	
(iii) On ART ≥ 6 months with no periods of defaulting on treatment since the last VL result (ART default defined as missing 7 or more consecutive days of ART	
(iv) On first-line ART regimen (substitutions within the first-line regimen prior to the last VL test are permissible)	
(v) No ARV drug substitutions since the last VL result < 1,000 copies/ml and plasma or dried-blood spot VL < 1,000 copies/ml in a patient who has been on first-line ART for at least 6 months, with VL drawn within last 12 months of enrolment while patient is receiving ART	
To be excluded are those:	
(i) on any other ART line regimen	
(ii) with co-morbidities requiring more frequent facility visits	
(iii) ART substitutions since last VL test (iv) diagnosed with a WHO clinical stage 3 or 4 condition within the past 3 months	
(iv) pregnant or less than 12 months postpartum and breastfeeding mothers	
(v) participating in another study that involves dispensing interval, adherence, or retention or involves receiving medications	

### Study procedures: recruitment, screening and enrolment processes

Recruitment methods for this study will be comparable across clusters (health facilities) and are expected to rely on active identification and referral of stable patients, as defined in the inclusion criteria above through relevant study staff. Facilities will be randomized to either of the 3 arms and individuals will receive their first drug supplies to which the cluster has been randomly assigned at enrolment. However, after first dispensing of drugs at the facility, those randomized to the arm to which patients are to receive 3 and 6 monthly ART supply through CAGs and CAD will respectively receive their next ART refills through these community approaches and platforms. Only those randomized to the 3 monthly ART-supply at facilities will receive their next ART refill within facilities.

The process of consenting participant’s will be fully documented, and only individuals who are able to demonstrate understanding will be asked to provide written informed consent for study screening and enrolment.

All patients potentially eligible for the study would also be eligible for a VL test per the national ART guidelines if they had not previously had one in the last 12 months. Once the VL result is back, they will be re-screened for study eligibility when they return for their next routine visit. After enrolment into study, co-enrolment in other studies will not be allowed given the likelihood that this could interfere with the primary study endpoint of retention.

### Participant retention and withdrawal or termination from the study

As retention in care is a primary outcome for the study, once an individual is enrolled, there will be no additional efforts applied towards retaining them except for standard of care counselling and routine retention support offered by sites as per national guidelines. Study interactions with participants will be minimized through use of existing medical records to track patient outcomes. We will obtain informed consent to contact people after completion of the study to perform qualitative interviews and surveys of acceptability, cost and quality of life measures. Regardless of the participant retention procedures referenced above, individuals may voluntarily withdraw from the study.

### Study intervention: differentiated models of care for MMD of ART

#### Three month dispensing model at health facilities

Providers at facilities randomized to three-month dispensing will be expected to provide all enrolled patients with a 3-month supply of ART. All other aspects of care will be as standard of care for the enrolling clinic, though routine clinic visits will occur every 90 days instead of the standard of care interval. Information about ideal storage conditions for ART will be provided by the clinic.

#### Community ART group (CAG) model (3-month supply of drug)

Study participants enrolled at facilities in this arm will join new or previously existing CAGs or will already be members of a CAG. Their first 3-month supply of drugs will be at enrolment facility, whilst the next ART refills will be through CAGs. The CAG will consist of 4–12 participants, who live in a similar geographic location and who all attend the same health care facility. The members’ appointments will be synchronized to ensure their scheduled clinic visits will be on the same day. The CAG will nominate a CAG leader and will meet on a 3-monthly basis in the community at a venue of their choice to access treatment. Stable study participants will be required to have a clinical consultation and VL testing at the facility at 12 and 24 months after enrolment in the study. Each member of the CAG will collect their own 3-month supply of ART from the clinic on this day. Participants who become ill at any stage of the study will report to the clinic as soon as possible. A CAG representative will distribute the drugs to the other CAGs members at the CAG meeting on the same day or the following day. The dates of these visits need to be noted by the facility so that all drugs are pre-dispensed and ready at this visit date.

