#### Community ART distribution model by healthcare worker (6-month supply of drug)

Participants enrolled at facilities in this arm will be given a 6 months’ supply of their ARVs at study enrolment. Their next ART refill will be conducted in 6 months in the community at a health outreach or health post (halls, churches or kiosks). These encounters in the community will be on an individual provider-patient basis, not as part of a CAG. The ART refill will be conducted by a healthcare worker who has been appropriately trained and certified for dispensing ART to stable patients. Study participants’ adherence will be assessed at this community distribution point as well as screening for TB, pregnancy, and other common conditions. Patients found to have any conditions that cannot be managed in the community will be referred to the health facility for further follow-up. These participants will continue to receive 6 month refills in the community if they remain stable (i.e. have VL less than 1000 copies per mL). Stable participants will be required to have a clinical consultation and VL done at the facility at 12 months and 24 months after enrolment.

Co-trimoxazole (CPT) and isoniazid (IPT) will also be provided to all arms based on the assigned ART dispensing interval and Lesotho guidelines.

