### Entry visit/baseline procedures

For those that enrol, the following detailed data will be collected and recorded from clinical and medical record review: HIV history, HIV-related medications, date of ART initiation, prior adherence/VL data, socio-demographic data including age, gender, level of education, estimated distance and time to travel to clinic, employment status, disclosure status and marital status. Costing data (patient cost data) including travel costs to clinic, opportunity cost of time spent on medication pickup visits etc., will be recorded.

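### Only 3MC places each participant in a local group, so patients without nearby members may be under-enrolled there or counted not retained, biasing the 3MC contrasts in a direction the protocol leaves open

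*Protocol article*

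**What the plan says.** The section on the community ART group model states: "Study participants enrolled at facilities in this arm will join new or previously existing CAGs or will already be members of a CAG". It then sets the size and make-up of a group: "The CAG will consist of 4–12 participants, who live in a similar geographic location and who all attend the same health care facility". The first supply is given at the facility on enrolment, and the group takes over from the next refill.

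The other two arms have no such condition. For control: "Providers at facilities randomized to three-month dispensing will be expected to provide all enrolled patients with a 3-month supply of ART". For 6MCD: "These encounters in the community will be on an individual provider-patient basis, not as part of a CAG".

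Eligibility is common to all arms: "The eligibility criteria of participants are tabulated in Table 1". That table has no criterion on where the patient lives or whether a group is available. It does require the patient to be "willing to participate in the MMD model (arm) that the patient’s study cluster has been randomized to", so enrolment follows cluster allocation. The Discussion says that participants and providers are not blinded. The recruitment section describes recruitment methods as comparable across facilities.

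Four other provisions bear on the point:
- *Setting* requires CAGs and distribution points to be feasible in each facility's community.
- *Study design* stratifies the randomisation by rural or urban facility.
- *Entry visit/baseline procedures* records "estimated distance and time to travel to clinic".
- *Statistical analysis* adjusts for baseline imbalances if any are identified, and names no covariate.

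*Study end points and definitions* counts a participant who is still in care but has left the assigned model, for whatever reason, as not retained.

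**The concern.** Each 3MC participant needs at least three suitable fellow patients nearby. A 3MF or 6MCD participant does not. Staff who know the allocation look for patients, and in one arm only they must also find a group. Randomising facilities does not balance who is enrolled within them after allocation.

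The Background names travel cost as a cause of poorer adherence and retention, so patients who are hard to place may plausibly also be harder to retain. With 5% expected attrition and a 3.25-point margin, small shifts in who is enrolled, or in how an unplaced patient is counted, can matter for the primary comparison of 3MC with 3MF. They can also matter for 6MCD against 3MC.

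**Working it through.** **Inputs from *Sample size estimate*.** Attrition 5%, margin 3.25 points, ICC 0.01, 10 facilities of 192 per arm (1920), one-sided α = 0.05, unpooled Z-test, power 85%.

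**The plan's own figure.**
- Per arm without clustering: n = 2 × 0.05 × 0.95 × (1.645 + 1.036)² / 0.0325² = 647.
- Design effect: 1 + (192 − 1) × 0.01 = 2.91. Then 647 × 2.91 = 1883 per arm, against 1920 stated.
- SE at equal rates: √(0.095 × 2.91 / 1920) = 1.20 points. Power = Φ(3.25/1.20 − 1.645) = 85.6%.

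The stated sample size reproduces and is not in question.

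**Assumed inputs.** The article gives neither the share f of patients without a possible group nor the ratio R of their attrition to that of other patients. Both are assumptions here.

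**Route 1: such patients enter 3MF but not 3MC.** Control attrition is 5% = a(1 − f + fR), where a is the attrition of placeable patients. The shift in favour of 3MC is 5% − a.
- f = 0.10, R = 2: a = 5/1.1 = 4.55%, shift 0.45 points (14% of the margin).
- f = 0.20, R = 2: a = 5/1.2 = 4.17%, shift 0.83 points (26%).
- Over f = 0.05–0.30 and R = 1.5–3: shift 0.12–1.87 points (4–58%).

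Error rate at the margin (true 8.25% against 5%):
- SE = √((0.05 × 0.95 + 0.0825 × 0.9175) × 2.91 / 1920) = 1.37 points.
- Shift 0.45: Φ(0.455/1.366 − 1.645) = 9.5%. Shift 0.83: Φ(0.833/1.366 − 1.645) = 15.0%. Nominal is 5%.
- If non-inferiority is read from the 95% interval in *Statistical analysis*, 1.96 replaces 1.645. The results are then about 5% and 9%, against 2.5% nominal.

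**Route 2: such patients enter 3MC, cannot be placed and are counted not retained.** If a share s is so counted, 3MC attrition becomes 5% + 0.95s. Power = Φ((3.25 − 0.95s)/SE − 1.645), with s in percentage points and SE recomputed at the new rate.

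| s | Added attrition (points) | Power |
|---|---|---|
| 0 | 0 | 85.6% |
| 1% | 0.95 | about 58% |
| 2% | 1.90 | about 27% |
| 3% | 2.85 | about 9% |

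**Balance of the two.** Route 2 cancels a route 1 shift of 0.45–0.83 points when s is about 0.45/0.95 = 0.5% to 0.83/0.95 = 0.9%, roughly 9 to 17 of 1920 participants. The sign of the net bias therefore turns on how few such patients are handled.

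**Objective (iii).** Here 3MC is the comparator, so both directions reverse. Route 1 works against non-inferiority of 6MCD and route 2 works for it.

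**The case against.** A reader might infer that isolated patients can enter control but not 3MC, and that objective (i) is therefore tilted towards non-inferiority. The document does not support either step. Table 1 excludes nobody on location. The CAG section describes what happens to patients already enrolled, allows new groups to form, and sets no distance for a similar location. Because the first supply is given at the facility, a patient could be enrolled before placement is settled. The endpoint rule then pushes the result the other way.

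The assumed shares may also be too high. The Background gives 25% adult HIV prevalence and 53% of adults on ART. If the 53% refers to infected adults, four patients on ART correspond to about 4/(0.25 × 0.53) = 30 adults. Not all of them would be stable or attend the same facility, but a 10–20% unplaceable share is not documented. Distance from the clinic is also not the same thing as lack of neighbours on ART.

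Facility-level CAG feasibility, rural/urban stratification, recorded distance and conditional adjustment all reduce the risk. They do not remove it. Feasibility and stratification act on facilities rather than on individual patients, and no adjustment restores patients who were never enrolled. What stands is the asymmetry between arms and the open direction; a proven bias towards non-inferiority does not stand.

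**Conclusion.** The point holds as a risk of bias of unknown sign. Only 3MC requires group membership tied to location, and enrolment follows an unblinded allocation. Patients without nearby members can then be lost to 3MC at recruitment or counted as failures after it. Under assumed shares of 10–20% and doubled attrition, the first route alone is worth 0.45–0.83 of the 3.25 points. Each 1% of 3MC participants counted not retained for lack of a group adds 0.95 points in the opposite direction. These figures show sensitivity and are not estimates, since the article gives no share, no risk ratio and no account of how such patients are handled.

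**What to change.** 1. In *Statistical analysis, power and sample size considerations*, replace adjustment that depends on finding an imbalance with pre-specified adjustment for distance and travel time to clinic in the primary GEE for every contrast. Report it beside the unadjusted result. State that distance is only a proxy for group availability and cannot restore patients never enrolled.
2. For the 3MC contrasts, log otherwise eligible patients at 3MC facilities who are not enrolled for lack of a group. This shows the size of the first route.
3. Record failure to form or find a group as a separate reason for leaving the model. Report a sensitivity analysis that separates 3MC participants counted not retained for that reason only.

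Do not add a placement screen to eligibility now. Recruitment began in August 2017 and was still open, so a screen would mix two populations and would ask unblinded control facilities for a hypothetical judgement.

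The cost is two covariates already collected, one log at the 3MC facilities, one reason code and one sensitivity analysis. The sample size does not change.
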